### Analytical plan

The datasets included for the analysis comprise results of the HDSS, clinical malaria surveys, cross-sectional malaria prevalence surveys and monitoring of mosquito densities. Malaria fever incidence is the primary outcome of the trial. Data are included up to the end of the next month after full intervention coverage was attained. For analyses of parasitological as well as entomological outcomes, intervention status is classified week by week on the basis of whether traps had been installed in the cluster. The whole study cluster is classified as intervened or non-intervened based on whether installation was complete in that cluster by the end of the week. Clusters are excluded from analysis during weeks in which some, but not all, of the households were provided with the intervention (i.e. during the week in which installations took place in that cluster). For malaria prevalence and incidence, the numbers and proportions of positive RDT tests were summarised by week and arm of the trial. For mosquito densities, rates of anophelines collected per trapping night were presented by week and arm of the trial.

Following the SWCRT design described by Silkey et al. [33], an analytical plan was constructed. The primary analysis of the impact of the trial on clinical malaria incidence, prevalence and vector densities follows two measures of effect: a contemporaneous comparison comparing the outcomes in intervened clusters with the not yet intervened clusters and a comparison of the final results in intervened areas with the baseline status. Generalized linear mixed models (GLMMs) with a binomial distribution will be deployed to carry out significance testing against the null hypothesis of no effect using a likelihood ratio test. For mosquito densities a GLMM will be used with a Poisson distribution. For analysis of medical and entomological data, random effects will be used to allow for spatial effects (cluster) as well as effects of round of surveillance (time period within cluster). Final models will consider possible confounding effects on the relationship between the intervention effect and measured outcomes. The analytical plan did not include any interim analyses.

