## Discussion

The long-term sustainability of malaria control achieved through the use of LLINs and case management with drugs is threatened by the development of insecticide and drug resistance. The SolarMal project has been designed to test for the first time whether mass trapping of mosquitoes can form a viable option for malaria control on Rusinga Island in Kenya, in addition to the already established LLIN plus curative strategy of the Kenyan National Malaria Control Programme (NMCP). The study took place in an area where LLIN coverage is high and drugs for case management are available and accessible.

The primary outcomes of the study will provide information about the efficacy of mass mosquito trapping on clinical malaria incidence, *Plasmodium* parasite prevalence, mosquito densities, EIR and sociological outcomes. A SWCRT design allows for before-and-after as well as contemporaneous measures of intervention effect, and clustering of the intervention permits measurement of a possible spill-over effect of traps into neighbouring non-intervened areas. Through gradual scale-up of intervention coverage over 2 years, with baseline measurements before the commencement of the rollout and at least 7 months of follow-up after completion of the rollout, an understanding of the time taken to achieve an impact through mass trapping will also be gained. By gathering data on multiple outcomes, i.e. human health and entomology, we anticipate that it will be possible to attribute an effect on malaria to the SMoTS intervention. Likewise, if the intervention is ineffective, it will be possible to offer explanations for this outcome. Understanding the mechanism behind a successful intervention will be vitally important in optimising the system for future scale-up and, in the instance of no observed effect, understanding this result will also allow improvements to the approach, which could lead to success in the future.

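### The primary analysis gives an uncontrolled final-versus-baseline comparison the same standing as the randomised contemporaneous comparison, and does not say which one is confirmatory

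*Protocol article*

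**What the plan says.** The Analytical plan section fixes the primary outcome clearly: "Malaria fever incidence is the primary outcome of the trial". It then says that "The primary analysis of the impact of the trial on clinical malaria incidence, prevalence and vector densities follows two measures of effect". The first measure is given as "a contemporaneous comparison comparing the outcomes in intervened clusters with the not yet intervened clusters". The second measure is given as "a comparison of the final results in intervened areas with the baseline status".

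The next sentence specifies generalised linear mixed models to "carry out significance testing against the null hypothesis of no effect using a likelihood ratio test", without saying to which measure the test applies. On adjustment, the section says that "random effects will be used to allow for spatial effects (cluster) as well as effects of round of surveillance (time period within cluster", and that "Final models will consider possible confounding effects on the relationship between the intervention effect and measured outcomes".

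Two other sections bear on the point. Study design attributes the design's ability to control for time to its contemporaneous controls. Randomising the intervention allocation says that all 81 clusters eventually receive traps. The article does not rank the two measures or say what follows if they disagree.

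**The concern.** The strength of a stepped wedge trial is its randomised order of crossover: at any time during rollout, treated clusters can be compared with clusters that are untreated by chance. The final-versus-baseline measure does not use that randomisation. Its two sides differ in trap status and also in everything else that changed across the island in about two years. Its null hypothesis can therefore be false when the traps do nothing.

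The article itself describes things besides traps that could change malaria over the period: treatment or referral of people found positive at the surveillance visits (Measurement of malaria incidence and prevalence), promotion of bed nets at every meeting and training session (Discussion), and intermittent indoor spraying in the region (Background). It does not claim that any of these did shift malaria on the island.

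At stake is which evidence carries the trial's main conclusion. With both measures in the primary analysis and neither put first, nothing in the text prevents a before-after difference from being read as the trap effect when the randomised contrast shows none.

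**Working it through.** **What each measure can identify**

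| | Contemporaneous | Final versus baseline |
|---|---|---|
| Comparator | clusters not yet intervened, same calendar time | same island, January to June 2013 |
| Allocation | randomised order | none; all clusters treated at the end |
| Island-wide change | common to both sides if calendar time is adjusted for | added to the trap effect |

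A random effect for cluster absorbs stable differences between places. A random effect for period within cluster absorbs local fluctuation and widens the standard error. Neither removes a shift that all clusters share. Measured covariates remove only the part of a shift that they explain. If round were instead coded as one effect common to all clusters, it would compete directly with the before-after contrast, so the behaviour of the planned test depends on coding that the article does not give.

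**The plan's own figures.** The article states no error rate for either measure. Its nearest figures are the detectable reductions in prevalence: 27 % from one survey and 11 % from six. The second follows from the first (27/√6 = 11.0). With a simple two-sided 5 % comparison the first comes out at 31.3 % if 907 is the total and 22.6 % if it is per group, so it is neither confirmed nor shown wrong. The point below does not depend on it.

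**Illustration on prevalence, with no trap effect**

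- From the article: baseline prevalence p₁ = 0.237; n = 907 as the minimum survey size; about 2,334 as 10 % of 23,337.
- Assumed: a relative decline d unrelated to traps, one survey at each end, two-sided 5 % level, design effect D.
- Formula: p₂ = p₁(1 − d); SE = √{D[p₁(1 − p₁) + p₂(1 − p₂)]/n}; probability of a significant decline = Φ[(p₁ − p₂)/SE − 1.96].

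For d = 0.20, n = 907, D = 1: p₂ = 0.1896; SE = √(0.3345/907) = 0.0192; z = 0.0474/0.0192 = 2.47; Φ(0.51) = 0.69.

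| Assumed decline | n per survey | D = 1 | D = 1.5 | D = 2 |
|---|---|---|---|---|
| 10 % | 907 | 23 % | 17 % | 14 % |
| 10 % | 2,334 | 49 % | 35 % | 28 % |
| 20 % | 907 | 69 % | 52 % | 42 % |
| 20 % | 2,334 | 98 % | 90 % | 80 % |

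With no decline, the figure in the benefit direction is 2.5 %.

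**Clinical incidence.** The article gives no baseline incidence. With 7,914 persons per period and an assumed risk of 0.6 % per visit, declines of 20 %, 30 % and 40 % give 18 %, 36 % and 59 %. At an assumed 0.31 % they give 11 %, 21 % and 35 %. The problem is smaller than for prevalence at the same decline, but present.

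**Both measures side by side.** A simulation with no trap effect used 81 clusters, 8 surveys, 11 persons per cluster and survey, an assumed between-cluster SD of 0.3 on the logit scale, crossover order randomised over all clusters, and 2,000 runs. It counted significant benefit claims on prevalence.

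| Assumed decline | Contemporaneous, cluster- and period-adjusted | Either measure suffices |
|---|---|---|
| 0 % | 3.4 % | 5.9 % |
| 10 % | 2.1 % | 25 % |
| 20 % | 2.4 % | 71 % |

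The contemporaneous contrast stays near its nominal 2.5 % whatever the decline; the either-measure rule does not. The simulation ignores the metacluster ordering and spill-over. The either-measure rule is a hypothetical, not something the article states.

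**The case against.** The strongest defence is that the before-after measure has a purpose. The article expects spill-over in both directions between intervened and neighbouring clusters, which can dilute the contemporaneous contrast. It also aims at elimination and wants the effect followed up to mass coverage. At full coverage no concurrent control exists, so only a comparison with baseline describes that state. This stands as a reason to keep the estimate. It is not a reason to give a non-randomised contrast equal standing with the randomised one.

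Several stronger readings are tempting, and the documents do not support them:

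- *Each measure has its own efficacy test, and either can declare success.* The test sentence follows both measures without restriction, but it does not say that each is tested separately, and no success criterion is stated. The full protocol or analysis plan may hold one. What can be said is that the text shown does not prevent such a claim.
- *Season is fully confounded with the traps.* Baseline ran January to June 2013, rollout finished in mid-2015, and data stop at the end of the month after full coverage. The two ends fall at roughly similar times of year. Differences between years remain.
- *Other control measures are ignored.* Net use, spraying, eave screening, socio-economic and environmental data are collected, and confounding is to be considered. An unmeasured island-wide trend remains.
- *The primary outcome is undefined.* The objectives and the Analytical plan both make clinical malaria incidence primary, and prevalence and vector density are listed as secondary objectives. The Discussion sentence beginning "The primary outcomes of the study will provide information about the efficacy of mass mosquito trapping on clinical malaria incidence" uses the plural loosely and goes on to several outcome groups; that is editorial.
- *Two tests raise the error to 9.75 %.* That figure (1 − 0.95²) is two-sided and assumes independence, whereas the two measures share data. In the benefit direction, independence would give 1 − 0.975² = 4.9 % against 2.5 %.

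**Conclusion.** The concern holds as a matter of standing. The primary analysis sets an uncontrolled before-after comparison beside the randomised contrast, leaves the test of no effect open to both, and gives neither priority. Following the text as written would let an island-wide change between 2013 and 2015 count as a trap effect.

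The size is conditional. A 20 % decline in prevalence unrelated to traps would give a significant before-after result with probability about 69 % at 907 per survey, or 42–52 % with design effects of 2 to 1.5; a 10 % decline would give 14–23 % over design effects of 2 to 1. These figures use a secondary outcome, an assumed decline, and a z test in place of the planned mixed model. The article gives no island trend for the period, so they show what could happen, not what did.

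**What to change.** In the Analytical plan, name the comparison of intervened with not-yet-intervened clusters on clinical malaria incidence, adjusted for calendar time, as the sole confirmatory analysis. Report the final-versus-baseline comparison as supportive, with an estimate and interval, and state that no efficacy claim rests on its test. Keep it, and give the reason: it describes the effect at full coverage and where spill-over blurs the concurrent contrast. As an editorial change, bring the plural use of primary outcomes in the Discussion into line with the stated objectives and the Analytical plan.

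This changes wording only. The trial status section says rollout is complete, and the article speaks of the models as still to be run, so no design element or data collection is affected. There are two real costs: spill-over may attenuate the contrast that now carries the conclusion, and the sponsor gives up an efficacy claim from the before-after test alone.

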### Study design

The SolarMal trial used a stepped wedge cluster-randomised trial (SWCRT) design [32] where the intervention is allocated to geographically defined clusters in a randomised order until full coverage is achieved. This trial design is appropriate for a vector control intervention such as an odour-baited trap which is expected to have an impact that extends to an area beyond the house on which it is installed (spill-over effect). Replication of the intervention in multiple clusters while maintaining contemporaneous control areas can be achieved with a cluster-randomised trial (CRT) design, typically aiming to reduce infection at the individual level by targeting a whole community/area with the intervention. The stepped wedge design provides the opportunity of attaining area-wide coverage and group randomisation by the gradual crossover of all clusters to the intervention arm. In this way the effect of the intervention can be measured when used at a relatively small scale, up to mass coverage. Given the contemporaneous controls, the stepped wedge design also allows some ability to control for time.

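### The primary analysis pairs the randomised comparison with a final-versus-baseline comparison that cannot separate traps from calendar time, and does not say which one carries the causal claim

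*Protocol article*

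**What the plan says.** In the protocol article, Analytical plan, the outcome is clear: "Malaria fever incidence is the primary outcome of the trial". The same section says that the primary analysis of clinical incidence, prevalence and vector density "follows two measures of effect: a contemporaneous comparison comparing the outcomes in intervened clusters with the not yet intervened clusters", and also "a comparison of the final results in intervened areas with the baseline status". Mixed models are then to be used for "significance testing against the null hypothesis of no effect using a likelihood ratio test". Random effects are planned for cluster and for "effects of round of surveillance (time period within cluster"). Possible confounders are to be considered in the final models, without further detail.

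The Primary objective names the outcome but no contrast. Study design states where control for time comes from: "Given the contemporaneous controls, the stepped wedge design also allows some ability to control for time". That statement is correct, and it applies to the first measure only. Power and sample size rationale bases the minimum detectable effect on one visit per person, halfway through the rollout.

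**The concern.** The two measures do not have the same standing. In the contemporaneous comparison, randomised order decides which clusters have traps at a given date. The final-versus-baseline comparison has no concurrent control, because every cluster has crossed over by the end. Anything that changed malaria across the island between the two dates is counted as trap effect.

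The article itself makes such change plausible. There are two rainy seasons a year (Study area). The baseline round ran from January to June 2013 (Demographic surveillance), and the rollout ended in mid-2015 (Discussion). People found RDT-positive in surveillance were treated throughout (Measurement of malaria incidence and prevalence), and bed net use was urged at all community meetings and training sessions (Discussion).

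The conclusion of the trial is at stake. A null randomised comparison together with a background decline could be reported as a significant primary result. A background rise could hide a real effect.

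**Working it through.** **1. Inputs.** From the article: 81 clusters; population 23,337 (about 288 per cluster); 80 % power for a 52 % reduction in incidence with effective n 7914. Assumed: two-sided alpha 0.05, and the size of any background change. Neither is in the article.

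**2. The plan's own figure.** The article gives no baseline incidence, so the 52 % cannot be reproduced directly. It can be solved for the risk per visit, p, that it implies:

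n per arm = (1.96 + 0.84)² × [p(1−p) + 0.48p(1−0.48p)] / (0.52p)²

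- 7914 per arm: p = 0.54 %.
- 7914 in total, 3957 per arm: p = 1.08 %.

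Both readings are carried forward. The power figures themselves are not disputed here.

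**3. Final-versus-baseline test with no trap effect.** Let risk p₀ fall to p₁ for reasons unrelated to traps, with n persons per period, d = p₀ − p₁, and p̄ the mean of the two risks:

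P(reject) = Φ[(d − 1.96·SE₀)/SE₁] + Φ[(−d − 1.96·SE₀)/SE₁]

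with SE₀ = √[2p̄(1−p̄)/n] and SE₁ = √{[p₀(1−p₀) + p₁(1−p₁)]/n}.

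Example: p₀ = 0.54 %, n = 7914, 20 % fall. Then d = 0.00108 and SE₀ ≈ SE₁ ≈ 0.00111, so P(reject) = 16 %.

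| Risk per visit, n per period | No change | 10 % fall | 20 % fall | 30 % fall |
|---|---|---|---|---|
| 0.54 %, 7914 | 5 % | 8 % | 16 % | 33 % |
| 1.08 %, 7914 | 5 % | 10 % | 28 % | 57 % |
| 1 %, 23,337 | 5 % | 20 % | 63 % | 94 % |

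The last row uses a rounded risk of 1 %. At 1.08 % its last two entries are 66 % and 96 %.

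**4. Check by simulation.** The set-up was 81 clusters over 8 rounds, about 294 persons per cluster-round, risk 1 %, cluster SD 0.4 and cluster-by-period SD 0.2 on the logit scale, and 2000 replicates. A Gaussian analysis stood in for the mixed model. For falls of 0, 10, 20 and 30 %, the final-versus-baseline test rejected in 4, 19, 62 and 93 % of replicates. The period-adjusted contemporaneous test stayed at 4–6 % throughout.

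**5. Random rather than fixed background change.** If each period carries an island-wide log-scale shock with SD s, then P(reject) = P(|Z| > 1.96/√(1 + 2s²/SE²)).

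- At 0.54 % and n 7914, SE = √[2 × 0.9946/(0.0054 × 7914)] = 0.216. For s = 0.05, 0.10, 0.20 and 0.30 the rates are 6, 10, 24 and 37 %.
- At 1.08 %, 81 × 288 = 23,328 persons and an assumed cluster-by-period SD of 0.3, SE = √[2/(23,328 × 0.0108) + 2 × 0.3²/81] = 0.101. The rates are 11, 25, 51 and 65 %.

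**6. Does the planned time effect help?** Read literally, it is separate for each cluster. Such an effect widens the standard error for variation between clusters but does not absorb a shift common to all 81. If the round effect were instead shared by all clusters and only two rounds were compared, the likelihood ratio statistic would be ln(t²) + 1. Rejection then needs t² > e^(3.84−1), that is |t| > 4.14. Across the three rows above, a 20 % fall is then rejected in 0.1–3 % of trials, a 30 % fall in 0.4–27 %, and a 50 % fall in 7–98 %.

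**7. Multiplicity alone.** Two valid, independent 5 % tests give at most 1 − 0.95² = 9.75 %. The larger figures come from confounding with time, not from the number of tests.

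**The case against.** A reader might infer that the plan holds two equally ranked p-values, either of which suffices, and that the error rate is far above 5 % whatever happens. The document does not support either inference. It speaks of two measures of effect and of a likelihood ratio test in the singular. It assigns no separate p-value and does not say that one success is enough. The error rate is 5 % when nothing else changes, and it is strongly raised only under background changes that the article does not quantify.

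A statistical analysis plan that is not shown may name the deciding test. That is possible, but the article itself fixes both measures as the primary analysis, so this is a choice made in the text and not a detail left out of it.

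The round effect can be read in two ways, and under the shared reading inflation is much smaller for modest change (step 6). Even then the comparison is not randomised. Covariates on nets, spraying, socio-economic status and environment were collected, which helps. Adjusting for measured covariates still cannot separate two variables that coincide completely.

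The most substantial point concerns purpose. The trial asks what mass coverage does, and the section on randomising the allocation expects spill-over at cluster edges in both directions. That may dilute the contemporaneous contrast, while final-versus-baseline is the only measure at full coverage. This is a good reason to report final-versus-baseline with its uncertainty. It is not a reason to let it decide.

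**Conclusion.** The concern holds in a limited form. The article places a randomised and an unrandomised measure together in the primary analysis, plans significance testing, and does not say which supports the causal claim. The final-versus-baseline measure is fully confounded with calendar time, and the power rationale does not cover it.

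The consequence is conditional. With an assumed island-wide fall of 20 % and no trap effect, a test of that measure rejects in about 16–63 % of trials; with a fall of 30 %, in about 33–94 %. These figures assume a two-sided 5 % level, a risk per visit of 0.54 % to about 1 %, between 7914 and about 23,300 persons per period, and a round effect specific to each cluster. With no background change the rate is 5 %.

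**What to change.** Amend the Analytical plan to read:

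> The primary test is the contemporaneous comparison, adjusted for calendar period, of clinical malaria between intervened and not-yet-intervened clusters. The final-versus-baseline comparison is secondary and supportive: it is reported as an estimate with a confidence interval beside the full series of rounds, and does not by itself support a claim that the traps worked.

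This takes two sentences and no new data. It fits the stated power basis, which already concerns a mid-rollout comparison. The downside is that the only full-coverage measure becomes supportive. Because spill-over may dilute the contemporaneous contrast, a null primary result should be interpreted with that in mind.

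Splitting alpha is not a substitute. At 0.025 for each measure, power for a 52 % reduction falls from 80 % to 71 % and the detectable reduction rises to 56 %, while the confounding with time remains.

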#### Secondary objectives

The medical objectives are as follows (all outcome measures include contemporaneous comparison of intervened with non-intervened areas, as well as before-and-after measures of intervened areas compared with baseline):To determine the impact of mass mosquito trapping on malaria prevalence measured by RDT, with subsequent high-resolution melting PCR used to estimate the prevalence of sub-patent malariaTo calculate differences in both measured and reported all-cause fevers following the introduction of odour-baited traps

The entomological objectives are as follows (all outcome measures include contemporaneous comparison of intervened with non-intervened areas, as well as before-and-after measures of intervened areas compared with baseline):To assess whether the mass trapping of mosquitoes reduces the population density of malaria vectors on Rusinga IslandTo determine whether the mass distribution of odour-baited mosquito traps leads to changes in mosquito species compositionTo record changes in entomological inoculation rate associated with implementation of the interventionTo compare mosquito densities and species composition indoors and outdoors

The sociological objectives are as follows:To determine the behavioural, socio-cultural and organisational factors that influence the effective and sustainable use of SMoTSTo foster learning relevant to adapting the implementation and sustainability strategy as an integral component of the interventionTo understand how the introduction and use of SMoTS affects and/or is affected by the use of other malaria control interventions

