### Entomological data collection and evaluation

Monitoring of mosquitoes began in September 2012 and continued until November 2015 (see Figs. 1 and 2). Sampling of mosquitoes at houses was performed using Mosquito Magnet-X® traps (American Biophysics Corporation, North Kingstown, RI, USA), baited with the same blend of five chemicals that are used for the intervention [10] and carbon dioxide produced by yeast and molasses fermentation [36]. For each round of sampling, 80 households were randomly selected with replacement from the active database maintained by the HDSS. In common with data collection in other arms of the project, random selection of households for entomological monitoring enabled measurement of entomological outcomes across the island throughout the duration of the SWCRT. Working four nights a week, ten houses were sampled every night with traps set at dusk (between 17:00 h and 18:00 h) and collected after dawn (between 07:00 h and 08:00 h). Each house was sampled once inside the house and once outside, with the inside/outside order randomised. The complete round of sampling took 4 weeks to complete, following which there was a 2-week period without sampling to make preparations for the next round. When a house had already been installed with a SMoTS, the Suna trap was disconnected during the two nights when the MM-X trap was used instead.

After collection of traps, mosquitoes were knocked down using a –20 °C freezer and identified to species group on the basis of morphology [37]. Specimens were separated and pooled by collection date, house of collection and inside/outside location, morphological species ID, sex and abdominal status. Pooled mosquitoes were stored in 80 % ethanol for subsequent molecular analyses: PCR for identification of *An. gambiae* s.l. complex and *An. funestus* s.l. complex [38, 39] and HRM-PCR for detection of *Plasmodium* DNA and blood meal analysis [35].

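### If the planned Poisson mixed model is also used to compare indoor with outdoor catches, it has no term for night-to-night extra variation, and the test rejects too often

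*Protocol article*

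**What the plan says.** The Analytical plan sets the distribution, the test and the random effects for mosquito counts:

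- Distribution: "For mosquito densities a GLMM will be used with a Poisson distribution".
- Test: "significance testing against the null hypothesis of no effect using a likelihood ratio test".
- Random effects, for medical and entomological data alike: "random effects will be used to allow for spatial effects (cluster) as well as effects of round of surveillance (time period within cluster").

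The models are introduced for two measures of effect. One is "a contemporaneous comparison comparing the outcomes in intervened clusters with the not yet intervened clusters"; the other sets final results in intervened areas against baseline.

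The Secondary objectives include an aim to "compare mosquito densities and species composition indoors and outdoors". No model or test is attached to that aim.

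The sampling scheme is in Entomological data collection and evaluation: "For each round of sampling, 80 households were randomly selected with replacement from the active database maintained by the HDSS". "Each house was sampled once inside the house and once outside, with the inside/outside order randomised". The two positions are therefore trapped on different nights at the same house.

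**The concern.** The indoor/outdoor contrast is made within a house, between its two trap nights. Cluster and cluster-period effects take the same value on both nights, so they drop out of the contrast and cannot absorb anything that differs between the nights. What is left is assumed to have variance equal to its mean. If catches at one house vary from night to night by more than that (weather, who slept where, trap performance), the standard error is too small. A likelihood ratio test relies on the assumed variance and does not correct for it.

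At stake is a named entomological objective: intervals would be too narrow, and an indoor/outdoor difference could be declared from noise. The Discussion relies on entomological results to explain why the intervention did or did not work.

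**Working it through.** **Inputs from the article.** "Working four nights a week, ten houses were sampled every night", over 4 weeks: 10 × 4 × 4 = 160 trap-nights per round. At two per house this is 160 / 2 = 80 houses, which reproduces the stated 80. With 81 clusters, that is about one sampled house per cluster per round.

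**Inputs assumed, because the article gives none.**

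- Two-sided 5 % level.
- Mean catch μ per trap-night: 0.1 to 3.
- Trap-night squared CV, c: 0.5 to 2.
- House squared CV, h: 0 or 1.
- Cluster-period SD on the log scale: 0.5.

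**Reduction of the test.** Each house contributes one indoor and one outdoor count to the same cluster-period, so every shared intercept cancels. The Poisson likelihood ratio test becomes a binomial test of total indoor against total outdoor catch. The true variance of the difference exceeds the assumed one by

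VIF = 1 + μ × R × c, with R = (1 + h) × exp(0.5²) = 1.284 × (1 + h),

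and type I error = 2 × [1 − Φ(1.96 / √VIF)].

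Example: μ = 1, c = 0.5, h = 0 gives VIF = 1 + 1.284 × 0.5 = 1.642, then 1.96 / 1.281 = 1.53, so 12.6 %.

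| Mean per trap-night | Lowest (c = 0.5, h = 0): VIF, error | Highest (c = 2, h = 1): VIF, error |
|---|---|---|
| 0.1 | 1.06, 5.7 % | 1.51, 11.1 % |
| 0.3 | 1.19, 7.3 % | 2.54, 21.9 % |
| 1 | 1.64, 12.6 % | 6.14, 42.9 % |
| 3 | 2.93, 25.2 % | 16.41, 62.8 % |

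Simulation of the same paired test gave 6–11 %, 7–21 %, 13–42 % and 26–62 %, within about one percentage point of the formula.

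**House variation alone.** With c = 0, VIF = 1 whatever h is. Simulation with house log-variance 0, 1 or 2 and no trap-night variation gave 4.0–5.5 %. House heterogeneity matters only as the multiplier R on c.

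**Intervention contrast.** With a random effect for each cluster and entomological round, simulated type I error was 3.5 % at mean 1 and 4.9 % at mean 0.25 (c = 2, house log-variance 1; 283 and 226 runs). Without that effect it was 58 % and 27 %. The stated period effect therefore protects this contrast.

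That protection depends on what a round means. An entomological cycle is 4 + 2 = 6 weeks, or 52 / 6 ≈ 8.7 a year, against three rounds of demographic surveillance (HDSS). A period defined by HDSS would hold 8.7 / 3 ≈ 2.9 entomological rounds. A small check with three rounds per period gave about 12 % at mean 0.3. It had only 120 runs, so the standard error is √(0.12 × 0.88 / 120) ≈ 3 percentage points.

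**The case against.** The strongest reply is that the plan never assigns this model to the indoor/outdoor contrast. It describes the models for the trial's impact, through two intervention comparisons, and for those the model performs at about its nominal level. The article also condenses a fuller plan and refers to final models still to be settled, so handling of overdispersion might be left there.

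Part of this stands. That the model covers indoor versus outdoor is an inference, so the point must be conditional. But the sentence on mosquito densities is unqualified and no other count model is offered. The distribution, test and random effects are stated choices, not omitted detail, and a better choice is available at little cost.

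Four stronger readings are tempting, and the documents do not support them:

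- A reader might infer one definite error rate, such as 20–50 %. That band corresponds to VIF from 2.34 to 8.44, and nothing in the article places the trial there.
- A reader might blame the missing house term. House effects cancel in a pair and cause no inflation alone.
- A reader might conclude that the trap-effect tests are invalid. With one entomological round per period they are not.
- A reader might extend the point to an indoor/outdoor-by-intervention interaction. The mechanism would carry over, but the article names no such test and none was simulated.

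**Conclusion.** The point holds in conditional form. If the stated Poisson model is used for the indoor/outdoor objective, its test is anti-conservative whenever catches vary between nights beyond Poisson. The direction follows from the sampling scheme and the listed random effects. The size rests on assumed values: close to nominal for sparse catches with mild dispersion, several times nominal for catches of one or more per trap-night with marked dispersion, and exactly nominal with none. Smaller cluster-period variation would lower the figures somewhat.

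The intervention contrast is sound if the period effect is one entomological round. It may be inflated if a period spans several rounds, but the evidence for that is one small simulation. The primary outcome, clinical malaria incidence, is untouched. This is a minor point on a secondary objective.

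**What to change.** Keep the Poisson model with its cluster and cluster-period effects, and add random intercepts for house-visit and for trap-night (observation level). Use it for all mosquito-density comparisons, and say that it covers indoor versus outdoor. State also that the period for entomological data is the entomological round.

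A negative binomial is an acceptable alternative only if it too carries a house-visit intercept. Without one it treats shared house variation as independent noise and loses the pairing. At mean 1 with house and night squared CV both 1, ignoring cluster-period variation:

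- True variance of the paired difference: 2 × (1 + 2 × 1) = 6.
- Variance the model assumes: total squared CV = 2 × 2 − 1 = 3, so 2 × (1 + 3) = 8.
- Consequence: intervals √(8/6) = 1.15 times too wide, and type I error about 2.4 %.

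The cost is a line in the analysis plan, one or two more variance parameters, and somewhat wider indoor/outdoor intervals. A sampled house is alone in its cluster-round about (80/81)^79 = 37 % of the time. There, house-visit and cluster-period effects cannot be told apart, so the two variances are separated by the remaining cluster-rounds.
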